### Study measurements and outcomes

#### Study measurements

The evaluation is comprised of a formative process evaluation and a summative evaluation, with the latter being a control group design (Table 2).

**Table 2 Tab2:** Summary of measurements and study outcomes

Measurements	Instruments	Group	Data Source	T0	in between	T1	Data analyses
Process evaluation							
Assessment of the intervention process from the view point of a resident	Focus group A	Intervention group	Resident		x		Qualitative analyses
Assessment of the intervention process from the view point of a caregiver/physician	Focus group B	Intervention group	Caregiver/physician		x		Qualitative analyses
Documentation of the implementation of pivotal intervention processes	Claims data	Intervention group	Health insurance company		x		Descriptive analyses
Organisational quality experienced the caregiver	Telephone interviews	Intervention group	Caregiver	x	x		Qualtitative and descriptive analyses
Summative evaluation							
Cost-based claims data from the German system of statutory health insurance (GKV)	Claims data	Intervention/control group	Health insurance company	x		x	Healthcare cost analyses, cost benefit analyses, cost-impact-analyses; propensity score adjustment
Audits and Peer-assessmen with caregivers							
a) Medical Quality	Audits and Peer-assessment of resident documens	Intervention group	Caregiver/physician		x		Qualtitative and descriptive analyses
b) Organizational Quality	Telephone interviews	Intervention group	Caregiver	x	x		Qualtitative and descriptive analyses
Quality experienced by the resident	Questionnaire	Intervention/control group	Resident		x		Comparison of intervention and control group using propensity score adjustment
Quality experienced by the caregiver/physician	Questionnaire	Intervention/control group	Caregiver/physician	x (intervention group)	x (control group)	x (intervention group)	Comparison of intervention and control group

T0 = baseline; T1 = 1 year after baseline

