Nursing staff are instructed to motivate residents to fill out all questionnaires and assist in case of lack of clarity of questions. However, no additional assistance (such as filling out forms on behalf of a resident or prompting answers) by nursing staff is allowed. In case residents do require additional assistance, residents’ relatives may be asked to assist filling out questionnaires. Any such assistance is to be documented on the questionnaire.

In addition to patient related processes, the intervention also includes organizational aspects that can only be monitored by nursing staff (e.g., the occurrence of interdisciplinary, indication-specific case conferences). Therefore, nursing staff and physicians will also complete a questionnaire (see also Additional files 5, 6, 7 and 8). Questions are based on work by Körner and Wirtz [25] assessing perceived teamwork of nursing staff and physicians, as well as a questionnaire regarding the working conditions of physicians by Fischbeck and Laubach [26] will be included and address physicians and nursing staff. Data will be collected at two time points: baseline (t0) and 12 months later (t1; Table 2). The control group will be questioned once. All questionnaire data will be assessed anonymously.

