#### Hypotheses

The hypothesis for health economic analyses is that the total cost of health care will be lower in the intervention group compared to the control group. Regarding quality of care, the hypothesis for patient reported outcomes is that perceived quality of care as well as overall satisfaction with received care in the NH is significantly better in the intervention croup compared to the control group, even after adjusting for relevant confounding variables. The hypotheses for nursing staff/physicians reported outcomes are that a) the perceived quality of medical/nursing care is significantly better in the intervention group compared to the control group; and b) the perceived quality of medical/nursing care is evaluated significantly better after conducting the intervention compared to baseline.

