#### Data analysis

Data will be collected from claims data, audits, telephone interviews, focus groups, and questionnaires (residents, nursing staff and physicians).

Claims data will be used to conduct economic analyses. It will be evaluated to what extent the claiming of benefits (indicators 1–5) differs between both groups regarding time and certain characteristics of the residents (age, gender, care level/care degree, dementia). Subsequently, cost indicators will be aggregated on a residential level. The resulting sum will equate the overall cost of the medical benefits claimed, including project costs. With a cost-benefit analysis, it will be examined to what extent the total cost differs between intervention and control group. Remaining differences between the two groups will be addressed using propensity score adjustment [27]. Results may also be used for budget-impact-analyses from a health insurance company’s perspective. Lastly, quality of life will be linked to the total cost of medical care with a cost-effectiveness analysis. Thereby, improvements in quality indicators such as ‘perceived quality of care’, ‘overall satisfaction with care’, ‘perceived state of health’ and ‘quality of life’ will be analyzed in relation to the costs of medical resource utilization by calculating incremental cost effectiveness ratios.

Because health care costs are not normally distributed, a generalized linear model (GLM) with a gamma distribution and log link transformation will be used for data analysis [28]. To account for the multi-level-structure of the data, a random intercept will be added on the regional or NH level. Finally, regression estimates will be converted back to costs for interpretation. Incremental cost effectiveness ratios and corresponding confidence intervals will be estimated using seemingly unrelated regressions [29].

For the peer assessment, the basis of valuation for the audits will be based on data in the CCC. For non-patient related organizational aspects of the intervention, data will be collected in telephone interviews. Both analyses will be integrated in the report.

Focus group interviews will be recorded. The content-analytical evaluation of the audio recordings will be based on an approach by Mayring [30] using the ATLAS.ti software [31]. The sample size was chosen based on experiences with previous multicenter studies.

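### The staff and physician survey has no time point common to both arms and no control baseline, so hypothesis (a) is non-concurrent and hypothesis (b) is uncontrolled

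*Protocol article*

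**What the plan says.** The Summative evaluation section of the protocol article describes the nursing staff and physician questionnaire: "Data will be collected at two time points: baseline (t0) and 12 months later (t1; Table 2"), followed by "The control group will be questioned once". Table 2 (Study measurements) shows when. In the row "Quality experienced by the caregiver/physician", the intervention group is marked at T0 and at T1, and the entry "x (control group") stands in the *in between* column. The table note reads "T0 = baseline; T1 = 1 year after baseline"; *in between* is given no date.

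Study outcomes places staff- and physician-perceived quality among the primary outcomes. The Hypotheses section attaches two superiority claims to it: (a) intervention better than control, and (b) perceived quality "evaluated significantly better after conducting the intervention compared to baseline". Under Data analysis, every test is run at α = 0.05. Homes enter an arm by location (Eligibility criteria and recruitment), so the arms are not randomised.

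**The concern.** A between-arm comparison of survey answers is interpretable if both arms are asked at the same time, or if each arm has its own baseline so that changes can be compared. The staff survey has neither. Changes in staffing, regulation or season between the control wave and an intervention wave enter the contrast for (a). So does any difference in working climate that already existed between the Tuebingen district and the rest of the state. Intervention homes also meet the questionnaire a second time at T1, while control homes see it only once.

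Hypothesis (b) uses the intervention group alone, although the summative evaluation is presented as a controlled comparison. Any one-year trend counts as benefit. At stake is whether a significant result on a primary outcome can be attributed to the intervention.

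**Working it through.** **What each contrast estimates.** Let μ be the control mean at T0, *g* the existing difference between regions, τ(*t*) the common time trend with τ(0) = 0, *s* the undated time of the control wave, *r* the effect of answering a second time, and δ the intervention effect at T1. The plan yields three means:

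- intervention at T0: μ + *g*
- control at *s*: μ + τ(*s*)
- intervention at T1: μ + *g* + τ(1) + *r* + δ

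The contrasts are then:

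- (a), if T1 is the intervention wave used: *g* + [τ(1) − τ(*s*)] + *r* + δ
- (b): τ(1) + *r* + δ
- intervention T0 against control: *g* − τ(*s*)

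Even with a linear trend, *s* known and *r* = 0, four unknowns (μ, *g*, the slope, δ) face three means, so δ is not identified without assuming something away.

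**What alternative schedules would estimate.**

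- Control wave at T1 only: (a) becomes *g* + *r* + δ. The trend is gone. The regional difference and the second-completion effect remain.
- Control waves at T0 and T1: the difference of changes is [τ(1) + *r* + δ] − [τ(1) + *r*] = δ, if trend and repeat effect are the same in both arms.

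**The plan's own sample size figures.** Design effect = 1 + 0.01 × (50 − 1) = 1.49, and 253 × 1.49 = 376.97, rounded up to 377; this reproduces. No effect size is stated for the 253. A two-sided two-sample t-test at α = 0.05 and 80% power gives 253 per group for an assumed d of 0.25 (252.13 rounded up); one-sided, about 198. The calculation uses about 50 observations per cluster, which matches 2000 residents in 40 homes. It therefore reads as a resident calculation. No staff sample size is given.

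**Illustration of the consequence.** Take δ = 0 and let *b* be the net non-intervention difference in SD units, that is *g* + τ(1) − τ(*s*) + *r*. With *n* independent respondents per group, SE = √(2/*n*) and

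type I error = 1 − Φ(1.96 − *b*/SE) + Φ(−1.96 − *b*/SE).

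For *n* = 253, SE = √(2/253) = 0.0889. For *b* = 0.10, *b*/SE = 1.125, so the error is 1 − Φ(0.835) + Φ(−3.085) ≈ 0.203. Across assumed values:

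| *n* per group (assumed) | *b* = 0 | *b* = 0.05 | *b* = 0.10 | *b* = 0.20 |
|---|---|---|---|---|
| 100 | 5.0% | 6.4% | 10.9% | 29.3% |
| 253 | 5.0% | 8.7% | 20.3% | 61.4% |
| 377 | 5.0% | 10.5% | 27.9% | 78.4% |

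Both *b* and *n* are assumptions. Allowing properly for clustering acts like a smaller *n* and moves the result towards the upper row. More respondents do not help: for a fixed bias, the false-positive rate rises with *n*.

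**The case against.** Data analysis names multilevel modelling and propensity score adjustment for questionnaire data, and subgroup analyses by professional group. It would therefore be wrong to infer that the staff comparison has no protection at all. Whether the propensity adjustment covers staff is unclear: Table 2 names it in the resident and claims rows but not in the staff row, and the text introduces it while discussing residents. If it is applied, it can reduce the part of *g* that is due to measured characteristics. It cannot remove a difference in survey timing, because timing and arm coincide.

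A reader might infer that (a) sets intervention answers at 12 months against earlier control answers, so that all drift between the two enters the estimate. The document does not go that far. The Hypotheses section does not say which intervention wave is used, and if homes start at different dates the calendar windows may overlap. What stands is that the control wave is scheduled at neither T0 nor T1. Placing it between two intervention waves does not repair this, since the extra T0 contrast is itself *g* − τ(*s*).

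It is also tempting to express a drift of, say, 0.10 SD as 40% of the effect of about 0.25 SD behind the 253. That divides an unsourced drift by an effect size back-solved from what reads as a resident calculation, and the document gives no staff equivalent.

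Finally, the row "Quality experienced by the resident" is also marked only *in between*, and Data analysis relates "improvements in quality indicators such as" perceived quality to costs. A reader might infer the same defect there. It does not follow: both arms are surveyed at the same scheduled point, the resident hypothesis is a between-group one, and the improvement can be read as the between-arm difference. Moving that wave later would trade against attrition, on top of an assumed 60% non-response.

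**Conclusion.** The point holds for the staff and physician questionnaire. As scheduled, the arms have no common survey point and the control group has no baseline, in a trial with regional allocation. Hypothesis (a) cannot separate the intervention effect from time trends and existing regional differences, and (b) is an uncontrolled before-after test. This follows directly from Table 2 and the Summative evaluation text and rests on no assumed figure.

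The size of the bias cannot be derived. The percentages above show only what assumed biases would do under assumed numbers of independent respondents. The cost outcome, with claims data at T0 and T1 in both arms, and the resident survey are outside this finding.

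**What to change.** - Field the single control staff survey in the same calendar window as the intervention T1 wave, show this in Table 2, and state that (a) is the T1 contrast, adjusted for measured staff and home characteristics.
- If one further control mailing is feasible, add a control T0 wave and test (b) as change relative to control. Because the questionnaires are anonymous, this would be a comparison of group changes unless respondents use a self-generated code. If a T0 wave is not feasible, report (b) as descriptive.
- If the control wave has already been fielded, report (a) as a non-concurrent, post-only comparison and not as confirmatory.

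The cost is a re-dated survey, or one extra mailing for the control T0 wave. It is small only if the control wave has not yet gone out, which the article does not say. If only T1 is aligned, intervention homes still answer for the second time and control homes for the first, and unmeasured regional differences remain; both should be stated as limitations.

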#### Study outcomes

Primary outcomes of the study are as follows: a) health economic analyses, including total cost of health care (assessment of cost related claims data of the statutory health insurance; pre-post measurement); b) quality of care analyses, including quality of care experienced by residents, physicians and nursing staff (questionnaires for residents, physicians and nursing staff; audits). Data will be included for the period of January 1, 2017 until September 30, 2020.

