### Research aims

In this paper, we present the study protocol of project CoCare, developed as a nursing home-based intervention to improve the coordination of medical care in long-term care NHs. Additionally, the study aims a) to optimize the collaboration of nursing staff and physicians in order to b) reduce the number of avoidable hospital admissions and ambulance transportations.

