##### Summative evaluation

The summative evaluation focuses on the effects of the intervention in terms of its quality and cost indicators compared to the control group.

On an individual level, the following cost indicators will be assessed via claims data: 1. Total cost of hospitalization; 2. Total cost of patient transport; 3. Total cost of outpatient treatments by GPs; 4. Total cost of outpatient treatments by medical practitioners; 5. Total cost of medication and medical supplies; 6. Assessment of additional cost for measures implemented in the intervention group. Cost-based claims data (indicators 1–5) is provided by the German system of statutory health insurance. Information about additional costs is gathered through intervention-related billing data (indicator 6). All claims data in the intervention and control group was pseudonymized and anonymized, respectively.

Regarding peer assessment, the quality of medical, patient related procedures will be evaluated by the ZGGF via audits. Patient related procedures include correct changing of a catheter within an instructed time. Non-patient related, organizational aspects of the intervention are assessed via telephone interviews by the Section of Health Care Research and Rehabilitation Research, Faculty of Medicine and Medical Center - University of Freiburg (see also Additional file 3). Questions include: “Are on-site visits by specialized physicians accompanied by assigned nursing staff?”

Furthermore, residents will be questioned about additional indicators of quality, including perceived quality of care (with a focus on medical care provided by GPs and cooperation of GPs and nursing staff), overall satisfaction with care in the NH, perceived state of health and overall quality of life. Since no available questionnaire is suitable for this particular intervention, a questionnaire assessing perceived quality of care will be developed. A number of instruments regarding overall satisfaction with care processes are available internationally [22]. However, only few validated and reliable measures are available in German. Hence, a modified version of the commonly used questionnaire “ZUF-A-7” [23] will be used in this study. Perceived state of health and overall quality of life is assessed using the (nationally/internationally) established World Health Organization Quality of Life Questionnaire - WHOQOL-OLD [24] (see also Additional file 4).

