## Discussion

Exploring and developing new interventions to improve living conditions of residents of long-term care NHs is crucial. Aside from detrimental effects on individual quality of life, the cost of long-term care NHs has become an increasing financial burden on society. Since a considerable number of hospitalizations could be avoided, this project will determine if improved coordination of medical care and an optimized collaboration of nursing staff and physicians can reduce the number of hospital admissions and ambulance transportations. To our knowledge, this study is the first to develop a complex intervention to positively and efficiently influence quality and cost of care in NHs as well as evaluate the intervention’s feasibility in a controlled design.

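### The stated aim is fewer avoidable admissions and ambulance transports, but the planned outcomes and analyses reach these events only through cost

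*Protocol article*

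**What the plan says.** The Abstract, Background and Research aims of the protocol article all give fewer avoidable events as the purpose; in Research aims the words are "reduce the number of avoidable hospital admissions and ambulance transportations". The Discussion turns this into a question the project will settle, namely whether coordination and collaboration "can reduce the number of hospital admissions and ambulance transportations".

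The measurement side is as follows.

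- Study outcomes: "Primary outcomes of the study are as follows: a) health economic analyses, including total cost of health care", and, as part b, "quality of care analyses, including quality of care experienced by residents, physicians and nursing staff".
- Hypotheses: the economic hypothesis is that "the total cost of health care will be lower in the intervention group compared to the control group". The others concern perceived quality and satisfaction.
- Summative evaluation: six individual-level cost indicators from claims and billing data, beginning "1. Total cost of hospitalization; 2. Total cost of patient transport". The sixth is the additional cost of the intervention measures.
- Data analysis: "It will be evaluated to what extent the claiming of benefits (indicators 1–5) differs between both groups". The indicators are then added up per resident, with project costs included, and the totals compared. For the model, "a generalized linear model (GLM) with a gamma distribution and log link transformation will be used for data analysis", with a random intercept at regional or nursing-home level and propensity score adjustment.
- Table 2: the claims-data row of the summative evaluation lists cost analyses only. No row lists admissions or transports.

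**The concern.** The aim and the Discussion sentence are about how many events occur. The outcomes, hypotheses and named model are about euros and perceived or audited quality. Hospitalization cost mixes the number of stays with the price and severity of each stay. It counts an avoidable stay and an unavoidable one alike, and transport cost has the same weakness.

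At stake is what the final report may claim. If hospitalization cost falls, the plan gives no basis for saying that residents were admitted less often, since the same fall could come from cheaper stays. If it does not fall, the plan gives no basis for saying that admissions were unchanged. The report would then have to draw its central conclusion, the one promised in the Discussion, from a quantity that does not determine it.

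**Working it through.** **1. Aim against measurement**

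| What the aim needs | What the article provides |
|---|---|
| Number of admissions | Hospitalization cost (indicator 1) |
| Number of ambulance transports | Patient transport cost (indicator 2) |
| Avoidable events told apart from others | No such split in the indicators |
| A hypothesis on either event | Hypotheses on total cost, perceived quality and satisfaction |
| An analysis suited to counts or rates | Gamma model with log link, for cost |

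**2. Why cost does not determine the count**

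Cost = number of events × mean cost per event, so the cost ratio between groups is the event ratio times the ratio of mean cost per event. The article gives no rate or unit cost, so the figures below are assumptions.

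- 20% fewer stays, mean cost unchanged: 0.80 × 1.00 = 0.80.
- Same number of stays, each 20% cheaper: 1.00 × 0.80 = 0.80. The cost result is the same, but no admission was avoided.
- 20% fewer stays, mean cost 25% higher: 0.80 × 1.25 = 1.00. A real fall does not show.

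Now suppose the avoided stays cost r times the average and nothing else changes. A 20% fall in stays then lowers hospital cost by 0.20 × r:

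| r (assumed) | Fall in hospital cost |
|---|---|
| 0.25 | 5% |
| 0.5 | 10% |
| 1.0 | 20% |
| 1.5 | 30% |

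With r = 0.5 the mean cost of the remaining stays rises by a factor of 0.90 / 0.80 = 1.125. The full masking in the third bullet would need r = 0, or a further difference between groups in price or severity. Selective avoidance of cheap stays alone therefore weakens the signal but does not erase it.

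**3. The plan's own sample-size figure**

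The design effect is 1 + 0.01 × (50 − 1) = 1.49, and 253 × 1.49 = 376.97, rounded up to 377 per group, as stated. Under a two-sided t-test at 0.05 with 80% power, 253 per group corresponds to a standardized difference of about 0.25. The article does not tie the calculation to a named endpoint, so it neither supports nor rules out an event outcome.

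**4. Would a count outcome be workable at 2000 per group?**

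With the article's design effect, the effective size is 2000 / 1.49 = 1342 per group. With event rate λ per resident-year, overdispersion k, one year of follow-up and rate ratio RR,

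SE(log RR) = √{[1/λ + k + 1/(λ·RR) + k] / effective size}.

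The detectable RR at two-sided 0.05 and 80% power solves −log(RR) / SE = 1.96 + 0.84. The values of λ and k are assumed.

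| λ | k = 0 | k = 1 |
|---|---|---|
| 0.3 | 0.81 | 0.79 |
| 0.6 | 0.87 | 0.83 |
| 1.0 | 0.90 | 0.86 |

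With an assumed intra-cluster correlation of 0.05, the design effect is 1 + 0.05 × 49 = 3.45, the effective size is 2000 / 3.45 = 580, and the detectable RR runs from 0.69 to 0.84 over the same grid. This approximation ignores deaths, attrition, baseline adjustment and the propensity score. It shows only that the planned size does not rule out a count outcome.

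**The case against.** A reader might infer that the trial cannot answer its own question at all. The documents do not support that, for three reasons.

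- Hospitalization and transport are separate indicators, and Data analysis says their claiming is compared between groups before anything is summed. That is indirect evidence on both events.
- The aim is broader than event reduction. Collaboration, quality and cost-effectiveness are also named, and the questionnaires, audits and cost analyses address them. Fewer admissions can be read as the route to lower cost and better quality, and cost is a legitimate primary outcome for a health-services evaluation.
- A reader might also infer that project payments would hide any fall in admissions. Those payments are indicator 6 and enter only the aggregated total; indicators 1 and 2 are free of them.

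Two further arguments carry weight. The claiming of benefits could be read as use of services. However, the indicators it refers to are defined as total costs, and neither of the first two has its own hypothesis. Also, an article condenses a fuller protocol, so secondary outcomes, a definition of avoidable and a count model may stand there. Their absence is for that reason not the finding. The finding is that the outcomes and hypotheses the article does state do not match the aim and the conclusion it also states.

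**Conclusion.** The mismatch stands. The aim and the Discussion sentence concern numbers of events, while the stated outcomes, hypotheses and analyses reach those events only through cost. Following the plan as written would support conclusions about hospitalization cost, transport cost, total cost and quality of care, but not a conclusion that admissions or transports became fewer, and still less that avoidable ones did.

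The size of the discrepancy cannot be computed from the article, which gives neither event rates nor unit costs. The 5% to 30% range for a 20% fall in stays is an illustration under assumed relative costs. The core point needs no such figure, because it follows from cost being a product of count and unit cost. It should be put right, but it leaves the cost and quality results intact.

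**What to change.** Name two secondary outcomes: hospital admissions and ambulance transports, each per resident-time, derived from the claims already obtained for both groups. Analyse them with a count or rate model that allows for time at risk and keeps the planned propensity score adjustment and random intercept, placed at nursing-home level. If the claims carry diagnoses, add a count of avoidable admissions from a diagnosis list fixed before any outcome data are seen.

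First check that stay-level and trip-level records and time at risk are supplied for both groups. The article calls the claims cost-based and says the control-group data were anonymized, so that these can be derived without new data is likely but not shown. The article also does not say that diagnoses are supplied. If event-level records are not held, restate the aim in the Abstract, Background and Research aims, and the matching Discussion sentence, in terms of cost and quality.

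The cost is two or three additional outcomes to analyse, a statement of where they stand in the testing plan, and the data check. Restating the aim costs only wording, but gives up the claim about event numbers.
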